**Figure 2 F2:**
[figure not shown]
Flowchart describing the inclusion and randomization of patients.

In both centers, we have, as a standard procedure, a separate file in which the product sticker of every placed stent is put, coupled with the name, birth date and patient number of the patient that received the stent. Neither the patient, nor the personnel who perform post-operative investigations, nor the analyst analyzing the data have insight in to this file; therefore keeping this file does not threaten the double-blind nature of this study.

The indication for breaking the randomization code is the need for open surgical or endovascular re-intervention if the treating physician feels this is required. The physician will then contact the coordinating or one of the principal investigators, who will reveal the type of stent and document breaking of the randomization code. Alternatively, this can be looked up in the separate file described in the previous paragraph.

### Study procedures

#### Digital Subtraction Angiography (DSA)

This is a widely used diagnostic technique to visualize peripheral arteries using fluoroscopy. A pre-contrast image is made, after which intra-arterial contrast is given proximal to the area that needs to be visualized. Using digital techniques, the pre-contrast image is subtracted from later images, thereby visualizing the degree of contrast in the arterial lumen without interference from bony or soft tissue structures.

#### Duplex Ultrasonography

This is a non-invasive diagnostic technique to estimate stenoses or occlusions in peripheral arteries. It incorporates two elements:

• Grayscale: Uses ultrasound to directly visualize the structure of the vessel. No motion or bloodflow is assessed. In this way, stenosis or occlusion can be directly visualized

• Color-doppler: Uses ultrasound to visualize the flow in the vessel. This is expressed as peak-systolic velocity (PSV), the highest velocity of the blood, during the systolic phase, in cm/sec. In a stenosis, the PSV will increase. When a stenosis is suspected, the peak-systolic velocity ratio is calculated. This is defined as the ratio of intra-stenotic PSV to pre-stenotic PSV. A ratio of >2.4 will be defined as a significant stenosis. When the vessel is occluded, no flow will be measured.

All study-related DUS are required to be performed in the vascular lab of the hospital by dedicated laboratory personnel who are blinded for the type of stent used.

#### ABI measurement

Systolic pressure in both arms is measured, using an automatic blood pressure monitor. The higher of the two will be used. Next, a blood pressure cuff is placed around the patient’s calf. Using a Doppler ultrasound device the dorsal pedal artery and posterior tibial artery are located. The blood pressure cuff is inflated until the Doppler signal disappears, and then slowly deflated. The pressure at which a Doppler signal reappears is documented for both arteries. The higher of the two is then divided by the systolic pressure in the arm. This is the ABI. When a standardized treadmill test (in patients with IC) is performed, this ABI measurement will be performed prior to the test (ABI in rest) and after completion of the test (ABI after exercise). All study-related ABI measurements are required to be performed in the vascular lab of the hospital by dedicated laboratory personnel who are blinded for the type of stent used.

#### Standardized treadmill test

Patients are required to walk at 3.2 km/h at a 12% grade for a maximum of 5 minutes on a treadmill. Claudication onset time (COT) will be measured (in minutes and seconds), which is defined as the time after initiation of exercise when the patients first experiences symptoms of claudication, and absolute claudication time (ACT), which is defined as the time after initiation of exercise until the patient cannot continue due to severe claudication pain. Patients with CLI are not required to undergo the standardized treadmill test. All study-related treadmill tests are required to be performed in the vascular lab of the hospital by dedicated laboratory personnel who are blinded for the type of stent used.

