## Background

Peripheral Arterial Occlusive Disease (PAOD) is a disease defined as reduced arterial blood flow to the lower extremities due to atherosclerotic arterial lesions and is diagnosed by an ankle-brachial index less than 0.9. It may lead to intermittent claudication (IC) or, with progression of the disease, critical limb ischemia (CLI). Only one out of every four to five patients with PAOD will be symptomatic [1]. The most common clinical manifestation of PAOD is intermittent claudication involving the pelvis, upper thigh and lower limb. It is defined as ischemic pain occurring during exercise, which is quickly relieved with rest (Fontaine II, Rutherford 1 to 3). CLI is a more severe presentation of PAOD, defined as ischemic rest pain (Fontaine III, Rutherford 4) or ischemic skin lesions: either ulcers or gangrene (Fontaine IV, Rutherford 5 and 6, respectively) [1]. See Table 1 for a description of the Rutherford classification. Patients presenting with CLI usually have multisegmental disease with involvement of the infra-inguinal arteries [2]. Ten to twenty percent of patients with IC will progress to CLI in the course of their disease [3-6]. The most important risk factors for progression to the advanced form of PAOD are age, tobacco use and diabetes mellitus [6].

**Table 1 T1:** Overview of the Rutherford-classification for PAOD

**Grade**	**Category**	**Clinical description**	**Objective criteria**
0	0	Asymptomatic - no hemodynamically significant occlusive disease	Normal treadmill test and ABI ≥0.9
	1	Mild claudication	Completes treadmill test. AP after exercise >50 mmHg, but at least 20 mmHg lower than resting value
I	2	Moderate claudication	Between categories 1 and 3
	3	Severe claudication	Cannot complete treadmill test *and* AP after exercise <50 mmHg
II	4	Ischemic rest pain	Resting AP <40 mmHg, flat or barely pulsatile ankle or metatarsal PVR, TP <30 mmHg
III	5	Minor tissue loss - nonhealing ulcer, focal gangrene with diffuse pedal ischemia	Resting AP <60 mmHg, ankle or metatarsal PVR flat or barely pulsatile, TP <40 mmHg
	6	Major tissue loss - extending above TM level, functional foot no longer salvageable	Same as category 5

AP = Ankle pressure, PAOD = Peripheral Arterial Occlusive Disease, PVR = pulse volume recording, TP = Toe pressure.

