#### Secondary endpoints

• Reocclusion rate. Defined as complete occlusion of the initially treated target-lesion.

• Target-lesion revascularization (TLR) rate. Defined as the rate and frequency of the need for repeated procedures (endovascular or open surgical) due to a problem arising from the target-lesion (+1 cm proximally and distally to include edge phenomena) in surviving patients with preserved limb.

• Immediate outcome:

– Procedural success. Defined as the combination of technical success, device success and absence of procedural complications.

– Technical success. Defined as successful vascular access and completion of the endovascular procedure and immediate morphological success with less than 30% residual diameter reduction of the treated lesion on completion and a systolic pressure gradient of less than 5 mmHg.

– Device success. Defined as exact deployment of the device, according to the instructions for use, using the assigned device only.

• Clinical outcome:

– Distribution of Rutherford stages during follow-up as compared to baseline.

– Functional outcome:

▪ In patients with IC: Improvement in claudication onset time (COT) and absolute claudicating time (ACT) on standardized treadmill test.

– Improvement in disease-related health status, functioning and quality of life. As defined by the Walking Impairment Questionnaire (WIQ) and RAND-36 questionnaire.

• Hemodynamic outcome:

– Mean and median ABI during follow-up as compared to baseline.

• Morphological outcome:

– Acute diameter gain (change in minimal luminal diameter from base-line to post-intervention.

• Target-extremity revascularization (TER) rate. Defined as the rate and frequency of the need for repeated procedures (endovascular or open surgical) due to a problem arising remote from the target-lesion in surviving patients with preserved limb.

• Mortality rate. Mortality rate associated with the endovascular procedure (that is, mortality within 30 days post-procedure or mortality during a hospitalization >30 days due to the procedure) will be reported separately, as well as overall mortality.

• Complication rate. In contrast with AE’s and SAE’s, which do not need to be related to the treatment, only complications that are (likely) related to the treatment will be reported. This is at the discretion of the investigator.

– Complications will be scored as ‘major’ or minor’. A major complication is a complication that:

▪ Leads to death;

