#### Parameters scored during regular follow-up

• Disease-related health status and quality of life: As defined by the Walking Impairment Questionnaire (WIQ) and RAND-36 questionnaire.

• Rutherford stage.

• Functional status:

– In patients with IC: Claudication onset time (COT) and absolute claudication time (ACT) on a standardized treadmill test (3.2 km/h at a 12% grade for a maximum of 5 minutes).

• Hemodynamic status:

– In patients with IC: ABI at rest and after standardized treadmill test;

– In patients with CLI: Systolic ankle pressure and ABI.

• Degree of stenosis and peak systolic velocity ratio on DUS.

• Occurrence of amputation.

• Mortality.

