#### Pre-operative

Pre-operative, DUS will be performed to document the occlusion or degree of the stenosis in the iliac and common femoral artery. This is mandatory, as this is the modality that will be used during follow-up. Additionally, either CT-angiography (CT-A) or MR-angiography (MR-A) of the entire lower extremity must be performed at the physician’s discretion. An ABI will be measured, including a treadmill test in claudicants. These are all part of our regular pre-operative work-up. In most cases, one or more of these investigations will have been performed prior to inclusion. When this has been no longer than 3 months prior to inclusion, the investigation will not have to be repeated for study purposes. All other relevant study parameters will be documented and patients will be asked to fill in the RAND-36 and WIQ.

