#### 1 month postoperative

At 1 month, patients will undergo an ABI with treadmill test (patients with persistent CLI will only require ABI measurement in rest). Any complication that occurred within the first 30 days will be scored. Patients will be asked to fill in the RAND-36 and the WIQ.

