#### 6, 12 and 24 months postoperative

At 6, 12 and 24 months, ABI and treadmill test will be performed, as well as a DUS, and patients will be asked to fill in the RAND-36 and WIQ. If DUS shows a stenosis, defined as a peak systolic velocity rate of ≥2.4, or is inconclusive, CT-A, MR-A or DSA will be performed. If an in-stent stenosis or occlusion is identified, this will be documented and treated within 1 month. Table 3 summarizes the study procedures at different moments.

**Table 3 T3:** Study procedures

	**Pre-ope-rative**	**Per-ope-rative**	**1 month**	**6 months**	**12 months**	**24 months**	**In case of restenosis**
DUS	X			X	X	X	X
ABI (with or with-out treadmill test)	X		X	X	X	X	X
DSA		X					X
WIQ/RAND-36	X		X	X	X	X	

DUS = Duplex ultrasonography, ABI = Ankle-brachial index, DSA = Digital subtraction angiography, WIQ = Walking Impairment Questionnaire, RAND-36 = RAND 36-Item Health Survey.

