#### Univariate analysis

Univariate analysis will be performed to assess differences in the other aforementioned primary and secondary endpoints.

Continuous data: Averages with standard deviation (parametric data) or medians with percentiles (non-parametric data) will be calculated. Differences between both groups will be tested using a Student’s *t*-test (parametric data) or a Mann–Whitney *U*-test (non-parametric data). Differences with a *P*-value <0.05 will be considered statistically significant. The following endpoints will be assessed:

Post-intervention COT and ACT;

Mean ABI.

Categorical data: Frequencies will be calculated and difference between both groups will be tested using Chi-squared test. Differences with a *P*-value <0.05 will be considered statistically significant. The following secondary endpoints will be assessed:

• Target lesion revascularization rate and target extremity revascularization rate;

• Procedural, technical and device success rate;

Mortality rate, complication rate, amputation rate;

• Rate of device-specific problems.

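### The treadmill testing rules and the planned test let membership of the COT/ACT comparison depend on disease state after randomisation

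*Protocol article*

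**What the plan says.** All places are in the protocol article.

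- *Secondary endpoints* defines the functional outcome: "In patients with IC: Improvement in claudication onset time (COT) and absolute claudicating time (ACT) on standardized treadmill test".
- *Pre-operative* asks for the baseline test only in claudicants: "An ABI will be measured, including a treadmill test in claudicants".
- *Standardized treadmill test* gives a general exemption: "Patients with CLI are not required to undergo the standardized treadmill test".
- *1 month postoperative* schedules the treadmill test and then says that "patients with persistent CLI will only require ABI measurement in rest".
- *6, 12 and 24 months postoperative* does not repeat the exemption: "At 6, 12 and 24 months, ABI and treadmill test will be performed, as well as a DUS".
- *Parameters scored during regular follow-up* ties the follow-up measurement to IC: "In patients with IC: Claudication onset time (COT) and absolute claudication time (ACT) on a standardized treadmill test".
- *Univariate analysis* lists the variable to be tested as "Post-intervention COT and ACT", with a t-test or, for non-parametric data, a Mann–Whitney test.

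Patients with IC and patients with CLI are both enrolled, since *Statistical analysis* names them as subgroups. The sections on withdrawal state intention-to-treat in general terms. They give no rule for a COT or ACT value that is missing because the patient has CLI.

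**The concern.** A between-arm comparison keeps the protection of randomisation only if the people compared are fixed by something known at randomisation. Here the rules allow a change of disease state during follow-up to decide who supplies a value.

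A patient randomised with claudication who worsens to CLI may have no treadmill result, so an arm with more such failures loses its worst walkers. A patient randomised with CLI who improves may be tested, so an arm that improves more CLI patients gains people who may walk less well than the original claudicants. Both shifts would count against the more effective stent.

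A difference between arms in these movements is not far-fetched. *Sample size calculation* expects 90% against 72% free of restenosis at 2 years, and *Background* says that "Ten to twenty percent of patients with IC will progress to CLI in the course of their disease". At stake is the reading of one secondary endpoint.

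**Working it through.** **Step 1. The rules side by side**

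| Patient | Baseline test | Follow-up test | Improvement calculable? | Can enter a comparison of post-intervention values? |
|---|---|---|---|---|
| IC at entry, still without CLI | Required | Yes | Yes | Yes |
| IC at entry, worsens to CLI | Required | Not required under the general exemption; scheduled without exemption at 6, 12 and 24 months | Only if tested | Only if tested |
| CLI at entry, improves | Not required | Yes at 1 month, since only persisting CLI is excused | No, without a baseline | Yes |
| CLI at entry, persists | Not required | Not required | No | No |

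The third row follows from the 1-month rule: the word persistent has a function only if CLI patients who improve are tested. The last two columns differ in that row because *Secondary endpoints* defines improvement while *Univariate analysis* tests post-intervention values.

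**Step 2. Illustration of possible size**

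The plan gives no figure for this endpoint, so there is none to reproduce. It also gives no CLI share, no rate of movement between IC and CLI, and no ACT values. Only the 87 patients per arm come from the document (*Sample size calculation*). Everything else is assumed:

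- CLI share at entry, p: 10% to 40%.
- Claudicants worsening to CLI, w: 2% covered; 2% or 10% uncovered.
- CLI patients improving, i: 80% covered; 80% or 50% uncovered.
- Mean ACT: 220 s in claudicants, 150 s in improved CLI patients, and 0 s assigned to worsened claudicants.

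Mean with the set fixed as IC at randomisation: (1 − w) × 220.

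Mean with the set given by status at the visit: [(1 − p)(1 − w) × 220 + p × i × 150] / [(1 − p)(1 − w) + p × i].

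Example with p = 20%, w = 2% against 10%, and i = 80% against 50%:

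- Set fixed at randomisation: 0.98 × 220 − 0.90 × 220 = 215.6 − 198.0 = +17.6 s for the covered stent.
- Status at visit, covered: (0.784 × 220 + 0.16 × 150) / 0.944 = 208.1 s.
- Status at visit, uncovered: (0.72 × 220 + 0.10 × 150) / 0.82 = 211.5 s.
- Difference: −3.3 s (from unrounded means).

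Over p = 10% to 40% (covered minus uncovered):

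| Movement, covered v uncovered | IC at randomisation | Status at visit |
|---|---|---|
| Equal (worsen 2% v 2%, improve 80% v 80%) | 0 s | 0 s |
| Worsen 2% v 10%, improve 80% v 80% | +17.6 s | +0.5 to +1.4 s |
| Worsen 2% v 2%, improve 80% v 50% | 0 s | −2.1 to −6.9 s |
| Both differ | +17.6 s | −1.8 to −5.8 s |

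Across these settings, patients without a required baseline form 5% to 37% of those tested in an arm, and about 1 to 8 worsened claudicants per arm go untested.

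The 17.6 s is simply (0.10 − 0.02) × 220 and exists only because worsened patients are scored 0 s. The third row does not depend on that scoring, because worsening is equal in the two arms.

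**The case against.** The strongest reply is that IC is a label fixed at entry. Improvement needs a baseline, which only entry claudicants must have. *Benefits and risks assessment* counts five treadmill tests for patients with IC; that equals the pre-operative test plus 1, 6, 12 and 24 months, and so fits patients who have IC from the start. The IC and CLI subgroups are also patient-level. On this reading, treadmill results of improved CLI patients would be collected but not analysed.

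Further, being excused from a test is not exclusion from analysis, and the later visits schedule the test without exemption. The progression figure in *Background* covers the whole disease course, not 2 years after stenting, and says nothing about CLI improving. An in-stent stenosis or occlusion is to be treated within 1 month, which may limit progression. Worsening is also recorded through Rutherford stage, amputation and repeat revascularization. Analysis sets are commonly left to an analysis plan.

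Much of this stands. A reader might infer that the endpoint set is whoever has claudication at the visit. No section says so, and the points above fit a baseline definition. Nor is it established that every worsened claudicant goes untested.

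What the reply does not remove is the conflict within the article. The 1-month rule goes by current state, the exemption has no time point, and the variable named for testing needs no baseline. An analysis plan could restrict the set, but it could not supply baseline tests that were never required. The Rutherford distribution is to be described without a statistical test, so it does not replace this comparison.

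**Conclusion.** The point holds as a gap that should be closed. The schedule and the planned test let membership of the COT/ACT comparison depend on disease state after randomisation, and they do not match an endpoint defined as improvement in patients with IC.

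Bias is conditional. If movement between IC and CLI differs by arm, the comparison can be distorted, probably against the better stent; this direction assumes that worsened claudicants and improved CLI patients walk less well than the remaining claudicants. If the movement is equal, there is no between-arm distortion.

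A reader might conclude that the randomised comparison is broken, or that a known number of seconds is lost. The document supports neither. The illustrated differences rest wholly on assumed rates and walking times, and the 17.6 s also on scoring worsened patients as 0 s. They show that a difference could vanish or change sign, not that it will. Only a secondary endpoint is affected.

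**What to change.** Reconcile *Secondary endpoints*, *Parameters scored during regular follow-up*, *Standardized treadmill test*, *Pre-operative*, the 1-month and later follow-up sections, and *Univariate analysis*, as follows:

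1. Define the COT/ACT analysis set as patients with IC (Rutherford 1–3) at randomisation, analysed as randomised.
2. Report treadmill results of patients randomised with CLI descriptively only.
3. State in advance how a value enters the comparison when it is unobtainable because of CLI or major amputation. One workable option is to give it the worst rank and use the Mann–Whitney test that the article already names; other conventions are possible.

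This changes wording only and needs no new visit or test. With the worst-rank option, the cost is that the result is read on ranks and not as a difference in mean seconds.

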#### Walking Impairment Questionnaire (WIQ)

The WIQ is a short, easy to fill out 14-item questionnaire that evaluates the degree of walking impairment in patients with intermittent claudication on three domains; walking distance, walking speed and the ability to climb stairs. These three domains represent common daily activities that are frequently impaired in patients with symptomatic PAOD and contribute to the degree of walking impairment. A Dutch translation, using the metric system, has been validated [57].

#### RAND-36 questionnaire

The RAND-36 questionnaire is a short, easy to fill out 36-item questionnaire, designed for scoring general quality of life and health status [58]. It is identical to the SF-36, but uses a slightly different scoring algorithm [59]. A translated Dutch version has been made, which has been validated [60]. It covers eight domains, and assesses these domains over the past 4 weeks. Domains can score from 0 to 100 points, with higher scores representing less physical limitation, fewer symptoms, greater treatment satisfaction, or better quality of life. The domains that are tested are: physical functioning, social functioning, physical role impairment, emotional role impairment, vitality, pain, mental health and general health perception. A separate question assesses health change with standardized response choices.

### Follow up scheme

During follow-up, any change in baseline characteristics, complication, or newly developed (re)stenosis or (re)occlusion will have to be documented as described in ’Endpoints/parameters’.

#### Pre-operative

Pre-operative, DUS will be performed to document the occlusion or degree of the stenosis in the iliac and common femoral artery. This is mandatory, as this is the modality that will be used during follow-up. Additionally, either CT-angiography (CT-A) or MR-angiography (MR-A) of the entire lower extremity must be performed at the physician’s discretion. An ABI will be measured, including a treadmill test in claudicants. These are all part of our regular pre-operative work-up. In most cases, one or more of these investigations will have been performed prior to inclusion. When this has been no longer than 3 months prior to inclusion, the investigation will not have to be repeated for study purposes. All other relevant study parameters will be documented and patients will be asked to fill in the RAND-36 and WIQ.

